### Randomisation

#### Participant allocation

Randomisation will be administered centrally by the Newcastle Clinical Trials Unit secure web-based system. Permuted random blocks of variable length will be used to allocate participants 1:1 to the control and experimental groups and ensure concealment of allocation from central trial staff. An individual not otherwise involved with the study will produce the final randomisation schedule. Stratification by three variables: (1) prior frequency of UTI: <4 episodes per year and ≥4 episodes per year, (2) a diagnosis of neurogenic lower urinary tract dysfunction: yes or no and (3) sex: female or male, will be performed prior to randomisation to ensure balanced allocation within these factors. For those allocated to prophylaxis an appointment will be arranged, facilitated by trial staff, with the prescribing clinician to commence prophylaxis. This may be a hospital consultant, a GP or a nurse specialist. Continued supply will be ensured typically through repeat prescription from the individual participant’s GP.

Patients may only be randomised into the study by an authorised member of staff at the study research site, as detailed in the delegation log.

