### Statistical analysis

An analysis of the primary outcome measure (incidence of UTI) for the full study will be performed both for the full data set and for the separate sub-groups defined by high and low baseline UTI rate (as specified during stratification for the randomisation process) using both the Poisson rate test and an incidence density ratio approach to allow for the different treatment durations; regression or generalised linear modelling approaches will be used to adjust for the effects of covariates. The model selection process will include the stratification factors (prior rate of UTI, presence of neurological disease and gender) and other baseline variables (person doing CISC [self or other], asymptomatic bacteriuria, age, type of catheter, use of antibiotic prophylaxis for UTI in the previous 12 months prior to randomisation and presence of bladder augmentation). The inclusion of interaction terms such as site will also be explored. The inclusion of baseline values as covariates will additionally enable the examination of possible interactions between effects observed and these values. Not all covariates mentioned above will be included in the final model, but all will be considered during the model selection process.

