### Sample size calculation

We plan to recruit 372 participants to the trial. Based on systematic reviews [11, 14] and expert (including patient) opinion, we believe that an overall 20 % reduction in symptomatic UTI rate from an average of 3 to 2.4 episodes per year represents the minimum clinically important difference. Using the Poisson rate test, completion of the study by 158 participants in each arm, 316 in total, would give 90 % power to detect this difference at the 5 % level. A total of 372 would allow for a 15 % attrition rate estimated from previous trials included in the systematic review. The attrition rate will be monitored and the sample size increased if necessary. Half this sample size would give 92 % power to detect a 25 % difference in the high frequency sub-group (from 4 to 3 episodes per year) and more than 99 % power for a 50 % reduction in the low frequency group (from 2 to 1) without allowance for multiple testing. We will approach approximately 750 eligible patients, anticipating a 50 % recruitment rate. We are currently recruiting from 52 sites which are coordinated through seven trial hubs. This number will be adjusted according to site and overall recruitment rate. For the qualitative sub-study of participant perception of benefit we will interview 30 trial participants who, at the time of trial consent, expressed a willingness to be interviewed at completion. We will create a purposive sample of approximately 20 participants from the prophylaxis arm and 10 from the no prophylaxis arm including some with neurological disease and some who did not complete the trial as allocated. We anticipate this will be sufficient to saturate themes arising from qualitative analysis of interview transcripts. For contingent valuation we will use a sample of 100 participants in each group; 200 in total will complete an exit questionnaire.

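### The covariate-adjusted primary analysis is left to a model selection that may drop the stratification factors, and no single analysis is labelled primary

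*Protocol article*

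**What the plan says.** Under Participant allocation, the protocol randomises 1:1 in permuted blocks, stratified by prior UTI frequency (below 4, or 4 and above, per year), neurogenic lower urinary tract dysfunction and sex. It says that stratification "will be performed prior to randomisation to ensure balanced allocation within these factors".

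The Statistical analysis section analyses the primary outcome "using both the Poisson rate test and an incidence density ratio approach to allow for the different treatment durations", and adds that "regression or generalised linear modelling approaches will be used to adjust for the effects of covariates". On how the adjusted model is reached, it says: "The model selection process will include the stratification factors (prior rate of UTI, presence of neurological disease and gender) and other baseline variables". The other variables are the person catheterising, asymptomatic bacteriuria, age, catheter type, prophylaxis in the previous 12 months and bladder augmentation. It continues: "The inclusion of interaction terms such as site will also be explored". It closes: "Not all covariates mentioned above will be included in the final model, but all will be considered during the model selection process".

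Study monitoring promises a documented SAP on which the steering and data monitoring committees may comment before analysis. Blinding says that central analysis staff will be unaware of allocation as far as possible.

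**The concern.** The stratification factors were considered important enough to balance by design. The Background also reports that the earlier systematic review asked future trials to control for sex, neurological cause and previous UTI frequency. Yet the analysis text treats these factors as candidates that compete for a place. The verb in the sentence about stratification factors governs the selection process, not the final model, and the closing sentence covers every covariate listed before it.

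Two things are at stake. First, an analysis that omits a prognostic stratification factor does not use the balance the design created, so a data-based standard error is larger than the design warrants. Second, a treatment estimate from a model chosen on the same outcome data is open to the charge, in an open-label trial, that the model was chosen for its result. Three named approaches without a declared primary one widen that freedom. The protocol analyses febrile UTI, microbiologically confirmed UTI, asymptomatic bacteriuria and hospitalisation analogously, so the rule carries over to them.

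**Working it through.** **1. The planned size.** The Sample size calculation section plans for a 20% reduction "from an average of 3 to 2.4 episodes per year represents the minimum clinically important difference", with 90% power at the 5% level. For a two-sided Poisson rate test, n per arm = (1.960 + 1.282)² × (3 + 2.4) / (3 − 2.4)² = 10.507 × 15 = 157.6, so 158. Then 316 / 0.85 = 371.8, so 372. Both figures reproduce, and nothing below changes them.

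**2. How much freedom the text leaves.** With 3 + 6 = 9 candidates there are 2⁹ = 512 main-effects models. Those keeping all three stratification factors number 2⁶ = 64, so 512 − 64 = 448 omit at least one. This counts what is allowed; it does not measure bias.

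**3. Would the strongest factor be dropped?** The subgroup planning rates are 4 and 2 per year. Assume equal strata of 158 and a uniform 20% reduction.
- Expected events: 79 × (4 + 3.2) = 568.8 in the high stratum and 79 × (2 + 1.6) = 284.4 in the low.
- SE of the log rate ratio = √(1/568.8 + 1/284.4) = 0.0726, so z = ln 2 / 0.0726 = 9.5.
- With an assumed gamma overdispersion of 0.4, SE = √(0.00527 + 2 × 0.4/158) = 0.102, so z = 6.8.

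No usual selection rule would remove a factor this strong. The factors at risk are those that predict little.

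**4. Effect on error rates.** The check was a simulation of 316 completers with stratified 1:1 allocation and nine binary candidates, 1,500 runs per scenario. The following are assumptions, not in the documents: covariate prevalences; prior UTI rate doubling the event rate, with weak effects for the other two strata; overdispersion 0 or 0.4; backward elimination at p < 0.10. Monte Carlo error near 5% is √(0.05 × 0.95 / 1500) = 0.6 percentage points.

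| Analysis | Type I error, no overdispersion | Type I error, overdispersion 0.4, scaled variance | Power at rate ratio 0.8, same overdispersed setting |
|---|---|---|---|
| No covariates | 4.8% | 3.0% | 52.9% |
| Three strata always in | 4.5% | 5.2% | 59.9% |
| Backward selection | 4.3% | 5.9% | 60.5% |
| Most extreme of 25 random subsets | 6.8% | 8.0% | not a valid test |

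Backward selection dropped at least one stratification factor in 77 to 93% of runs across all scenarios. Even so, its error rate and power stayed close to those of the model with the strata forced in. Omitting all strata made the scaled standard error conservative. Runs with overdispersion and an uncorrected Poisson variance are left out: type I error there was about 20% or more whichever covariates were used, which is a separate matter.

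**5. Site.** 316 / 52 = 6.1 completers per site, about 3 per arm. A treatment-by-site interaction would use 52 − 1 = 51 degrees of freedom.

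**The case against.** The strongest reply is that this is detail for the SAP, which is not shown. The SAP may fix the selection rule before analysis, so the choices need not be post hoc, and partial blinding of analysts gives some protection. This stands in part. But the article is not silent: it prescribes selection and rules out keeping every covariate. A SAP that followed it would still let the outcome data choose the model.

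A second reply is that the unadjusted Poisson rate test, on which the sample size rests, may be the headline result, with the selected model in support. The text allows this reading, so a reader should not conclude that the selected model is the primary analysis. It equally allows the opposite reading, and the Poisson rate test as named makes no use of the strata either.

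Two stronger inferences are tempting and are not supported.
- **That power falls from 90% to 84%.** With arm variances of 4 and 3.04, a robust SE is √(7.04/158) = 0.211 against a true SE of √(5.4/158) = 0.185. Power is then Φ((0.6 − 1.96 × 0.211)/0.185) = 84%. This needs prior UTI rate to be omitted although its z is about 9.5, and a robust standard error the plan does not name. It also assumes equal strata and a uniform 20% effect, whereas the protocol's own subgroup figures are 4 to 3 and 2 to 1. Under the named Poisson test in that setting, simulated power was about 89%.
- **That the p-value and interval are invalid.** Selection made without regard to treatment left type I error near 5%. Inflation needed deliberate picking, which the protocol does not describe.

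On site, the wording commits only to exploring interactions, not to placing 51 terms in the primary model.

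**Conclusion.** The point holds as a stated, inferior choice of method with modest consequences. The text lets the adjusted model omit factors used in the randomisation, makes its treatment estimate depend on data-driven choices, and labels none of its three approaches as primary.

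The likely cost is some loss of precision or a mildly conservative standard error if a prognostic stratum is left out. In the overdispersed scenario, omitting all three gave 3.0% type I error, and 52.9% power against 59.9%. Type I error rises, to about 7 to 8% in the assumed case, only if the model is picked with sight of the treatment result. These sizes rest on the assumed prevalences, effects, overdispersion and elimination rule. The textual finding rests on none of them.

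**What to change.** Replace the selection wording with one named primary analysis: a count regression with follow-up time as offset, containing treatment and the three stratification factors, always retained, with no variable selection. Fix any further covariates in advance, or move them to a single labelled sensitivity model. Label the remaining approaches as supportive. Treat any site interaction as exploratory only, outside the primary model. Apply the same rule to the secondary outcomes analysed analogously.

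The cost is wording in the protocol and SAP, agreed before analysis. It needs no new data, since the strata are recorded at randomisation, and no extra participants.

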## Background

Clean intermittent self-catheterisation (CISC) is a frequently used intervention for people who cannot empty their bladder effectively due to bladder outlet obstruction or failure of bladder muscle contraction which may be associated with neurological disease [1]. Patients needing CISC are taught how to insert a catheter, drain the bladder and then remove the catheter [2]. Single-use disposable catheters, typically with a hydrophilic coating, are predominantly used in the UK [3].

There are no accurate prevalence data for CISC use in the UK. The National Health Service (NHS) England prescription database recorded 47 million CISC catheter prescriptions in 2010 at a cost of £64 million [4]. If we assume each individual uses an average of 25 catheters per week, this suggests that there are about 36,000 CISC users in England and perhaps 43,000 in the UK as a whole. This estimate is in agreement with a primary care-based estimate which found a prevalence of approximately 7–8 per 10,000 adults, suggesting an approximate total of 43,000–49,000 adults in the UK ([name], personal communication, August 2011).

Recurrent urinary tract infection (UTI) is the commonest adverse event experienced by CISC users affecting between 12–88 % of studied cohorts [5]. Differentiation between asymptomatic bacteriuria, which would not normally be treated, and symptomatic UTI in these studies is difficult. One estimate suggests that 50 % of users have persistent bacteriuria and at least 25 % suffer two or more symptomatic UTI episodes per year [6]. Conservatively this suggests that up to 10,000 CISC users in the UK suffer recurrent UTI, the target population for this trial. Neurological disease, female sex, young age and high bladder volumes are associated with higher prevalence of UTI [1]. *Escherichia coli* (*E. coli*) is the causative bacterium in 60–70 % of cases [6]. Most episodes are associated with transient symptoms such as lower abdominal pain, urethral pain and flu-like symptoms; occasionally systemic upset can occur with fever and loin pain. Those with reduced bladder sensation may alternatively complain of cloudy urine, increased odour and incontinence [7]. Recurrent UTI is distressing and an additional burden for patients with underlying neurological disease and functional disability [5]. For some there is a risk of renal damage in the longer term [7] or significant sepsis requiring intensive care and potential mortality.

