#### Secondary objectives

The secondary objectives are as follows:Clinical○ Determine the relative effect on quality of life (QoL) amongst trial participants○ Measure overall satisfaction with prophylactic antibiotic treatment○ Assess participants’ perception of benefit at 12 months using qualitative methodology○ Record adverse effects related to both prophylaxis and treatment antibiotic use○ Determine relative rates of hospitalisation because of UTI○ Measure difference in renal function by estimated glomerular filtration rate (eGFR) at 12 months○ Determine rates of asymptomatic bacteriuria at 12 months○ Assess ecological change in *E. coli* isolated from urine and perianal swabsEconomic○ Measure incremental cost per QALY gained through repeated completion of SF-36○ Assess participants’ willingness to pay to avoid a UTI by contingent valuation at end of trial participation and incorporate these data in the economic evaluation using a cost-benefit framework.

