### Secondary outcome measures

Secondary outcome measures will be collected as additional criteria to the primary outcome from inspection of participant healthcare records, by participant questionnaire or by clinical test performed at specific time points. The following are also included.The rate of UTI will also be alternatively defined as the *incident density rate*; the number of UTIs suffered during the observation period minus days spent taking treatment courses of antibiotics active against urinary tract organisms.*Febrile UTI* defined as the primary outcome plus presence of a recorded fever of more than 38 °C:○ Confirmed by inspection of primary or secondary healthcare record by research staff.*Microbiologically confirmed symptomatic UTI* defined as the primary outcome plus positive urine culture:^1^○ Participants will provide an intermittent catheter specimen of urine for local analysis as requested by the treating clinician. This will be analysed according to clinician decision by the local microbiology using the local standard operating procedure (SOP). We will also ask the participant to send a urine specimen using provided safe packaging to the central microbiology trial laboratory in the Newcastle upon Tyne Hospitals NHS Foundation Trust each time they consider they have symptoms suggestive of UTI and intend to commence a course of antibiotic treatment. This will be analysed and cultured on receipt and the result used for trial outcome purposes but not for patient care.*Antibiotic prescription for asymptomatic UTI* without participant-reported or clinician recorded evidence of symptom change.*Asymptomatic bacteriuria* defined as a positive urine culture in the absence of symptoms.○ Participants will be asked to send a urine sample to the central laboratory at baseline prior to randomisation and during asymptomatic periods in months 3, 6, 9 and 12 of their trial participation. They will also be separately consented to provide a urine sample 6 months after completion of trial (18-month time point).*Hospitalisation due to UTI* defined as an unplanned visit to hospital for treatment of a UTI which required at least one overnight stay in hospital.○ Collected from healthcare record review and checked from participant report or enquiry.*Participant perception of benefit.*○ We will record and analyse semi-structured interviews with up to 30 participants purposively sampled from both trial arms on completion of their 12-month trial period.*Overall satisfaction with allocated treatment strategy.*○ Participants will complete the treatment satisfaction questionnaire for medication at 12 months as part of their completion of trial questionnaire [20].*Generic health-related quality of life.*○ Participant completion of the SF-36 1-week recall questionnaire at baseline, 3, 6, 9 and 12 months and within the first 2 days of each episode of symptomatic antibiotic-treated UTI [21].

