A number of additional secondary analyses will also be undertaken to examine the secondary outcome variables. Febrile and microbiologically confirmed UTI, asymptomatic bacteriuria and hospitalisation due to UTI will be analysed in a manner analogous to that for the primary outcome. Analyses of other outcomes will use similar regression or analysis of variance/covariance-based approaches as described above to compare between treatment groups while allowing for the effects of covariates. Baseline measures would be included in the analysis, either considered as possible covariates or by exploring changes in outcome measures from baseline. Analysis will be carried out primarily on an intention-to-treat basis, although other exploratory analyses such as per-protocol may also be considered. Data will be analysed at the end of the study; there are no planned interim analyses. Safety data will be regularly and frequently reviewed but will not be subjected to statistical analysis. Data with missing observations due to loss to follow-up will be examined to determine both the extent of the missing data and whether they are missing at random or are informative. If data are missing to a sufficient extent, the use of appropriate multiple imputation techniques will be considered.

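### Asymptomatic bacteriuria is assigned the primary outcome's event-rate methods although it is a yes/no culture on scheduled specimens, so person-time is the wrong denominator and the Poisson standard error can err in either direction

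*Protocol article*

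**What the plan says.** The Statistical analysis section of the protocol article sets the primary analysis as "using both the Poisson rate test and an incidence density ratio approach to allow for the different treatment durations", and adds that "regression or generalised linear modelling approaches will be used to adjust for the effects of covariates". No distribution is named for that adjusted model. For the secondary outcomes it then states: "Febrile and microbiologically confirmed UTI, asymptomatic bacteriuria and hospitalisation due to UTI will be analysed in a manner analogous to that for the primary outcome". The sentence that follows deals with the remaining outcomes as a separate class, by regression or analysis of variance or covariance. Asymptomatic bacteriuria has therefore been placed with the event-rate outcomes.

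Under Secondary outcome measures, asymptomatic bacteriuria is "defined as a positive urine culture in the absence of symptoms". Specimens are requested at baseline and "during asymptomatic periods in months 3, 6, 9 and 12 of their trial participation", with a separately consented one at 18 months. Table 1 shows the same schedule up to month 12.

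The Secondary objectives are worded differently: "Determine rates of asymptomatic bacteriuria at 12 months". That can be read as one specimen or as a summary over the year.

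The Background gives the only figure bearing on prevalence: by one estimate, 50% "of users have persistent bacteriuria".

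**The concern.** Febrile UTI, microbiologically confirmed UTI and hospitalisation are episodes that arise while a participant is under observation, so a count over person-time suits them. Asymptomatic bacteriuria is a state, looked for on a few set occasions. A participant can have at most four positive results after baseline, and the number depends on how many specimens are sent in.

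Two things follow if the named methods are applied as written.

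- **Denominator.** A rate per unit time treats a specimen that was never returned as though it were negative. Differences in specimen return then mix with differences in prevalence.
- **Variance.** A Poisson count has variance equal to its mean. A sum of a few yes/no results has less variance than that if the results are independent within a person, and can have more if they are strongly correlated.

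At stake are the confidence interval and p-value for a listed secondary objective, in a trial where the effect of prophylaxis on bacterial carriage is of interest in its own right.

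**Working it through.** **1. The primary method is a variance-equals-mean method.** With rates of 3 and 2.4 per year, 90% power and 5% two-sided (Sample size calculation section):

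n per arm = (3 + 2.4) × (1.960 + 1.282)² / (3 − 2.4)² = 5.4 × 10.51 / 0.36 = 157.6, so 158.

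316 / 0.85 = 371.8, so 372. Both stated figures reproduce. No figure is stated for asymptomatic bacteriuria.

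**2. Inputs for bacteriuria.**

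- k = 4 specimens after baseline (Secondary outcome measures), or k = 1 if month 12 alone is meant (Secondary objectives).
- p = 0.50 (Background), taken as the prevalence at each visit. Other values of p below are assumptions.
- rho, the correlation between two cultures from the same person: not given in the protocol. It is assumed over the whole range 0 to 1.

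**3. Formulae for the number of positive cultures per person.**

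- Poisson variance: kp
- Actual variance: kp(1 − p)[1 + (k − 1)rho]
- Ratio R of actual to Poisson: (1 − p)[1 + (k − 1)rho]
- Poisson SE relative to actual SE: 1/√R
- True type I error of a nominal 5% test: 2[1 − Φ(1.96/√R)]

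**4. Four specimens, p = 0.5.** Poisson variance is 4 × 0.5 = 2, actual variance is 1 + 3rho, and R = 0.5(1 + 3rho).

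| rho (assumed) | R | Poisson SE / actual SE | True type I error |
|---|---|---|---|
| 0 | 0.50 | 1.41 | 0.6% |
| 0.2 | 0.80 | 1.12 | 2.8% |
| 1/3 | 1.00 | 1.00 | 5.0% |
| 0.5 | 1.25 | 0.89 | 8.0% |
| 0.7 | 1.55 | 0.80 | 11.5% |
| 1 | 2.00 | 0.71 | 16.6% |

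A simulation with 158 per arm, four specimens each and 4,000 replicates per setting gave 0.4%, 4.7%, 7.9% and 16.0% at rho = 0, 1/3, 0.5 and 1, in line with the formula.

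**5. Other prevalences (assumed).** At p = 0.3 the type I error runs from 1.9% (rho = 0) to about 24% (rho = 1). At p = 0.7 it runs from 0.03% to 7.4%. The Poisson variance is exactly right where rho = p/[3(1 − p)]: 0.14, 0.33 and 0.78 for p = 0.3, 0.5 and 0.7.

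**6. Month-12 specimen alone.** With k = 1, R = 1 − p, so the Poisson SE is always too wide. At p = 0.5 it is 1/√0.5 = 1.41 times the actual SE, with a type I error of 0.6%.

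**7. Denominator, for illustration only.** Suppose true prevalence is equal in the arms, and participants return on average 3.2 specimens in the control arm and 3.6 in the prophylaxis arm (assumed numbers). A rate per person-year then gives a ratio of 3.6/3.2 = 1.125 with no true effect. Dividing by specimens examined gives 1.

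**The case against.** The strongest reply is that the protocol does not fix a Poisson model for this outcome. An analogous analysis need not be an identical one. The adjusted analysis is described as regression or generalised linear modelling, and a binomial model is one of those. The Study monitoring section promises a documented analysis plan, to be reviewed by the steering and monitoring committees; it is not shown here. This stands for the adjusted model. It does not cover the two methods that are named, which are both rate methods and carry no exception for bacteriuria.

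A reader might infer that the confidence intervals are bound to be wrong, or that about one test in six would be falsely positive. The documents do not support either. No within-person correlation is given. The description of bacteriuria as persistent suggests that rho is not near zero, but it supplies no value. At p = 0.5 the Poisson variance is exact at rho = 1/3, and for rho between 0.2 and 0.5 the SE is within about 12% of correct. The 17% figure requires that nobody's culture result changes over the year. If the objective means the month-12 specimen only, there is no repeated-measures problem and the literal test is conservative.

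A reader might also infer that specimen return will differ by arm because participants with more UTIs have fewer symptom-free periods. That is possible but not shown. At the planned control rate of 3 episodes a year and typical courses of 3 or 7 days, treatment takes up 3 × 3 = 9 to 3 × 7 = 21 days a year, so most participants should have a usable window. A binomial model on returned specimens would not by itself remove such a difference either.

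**Conclusion.** The mismatch is real: event-rate methods are assigned to a yes/no culture on scheduled specimens. Specimens examined should replace person-time as the denominator, whatever the correlation. The Poisson standard error can be too wide, too narrow or about right. At 50% prevalence with four specimens, the true type I error of a literal test lies between 0.6% and 17% across the full assumed range of rho. With the month-12 specimen alone it is 0.6%, with an SE 1.41 times too wide. These sizes rest on the single prevalence estimate in the Background, on an assumed rho, and on the Poisson test being applied as named.

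The protocol also leaves open whether one specimen or four are analysed, and this decides which of those results applies. This is a secondary outcome with no sample size attached to it, and the primary conclusion is unaffected.

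**What to change.** - Take asymptomatic bacteriuria out of the event-rate list in the Statistical analysis section. Keep febrile UTI, microbiologically confirmed UTI and hospitalisation there.
- State whether the month-12 specimen or all four post-baseline specimens are analysed, so that Secondary objectives and Secondary outcome measures agree.
- Use a binomial model: logistic regression for month 12 alone, or GEE or mixed-effects logistic regression if the four visits are used. Include treatment, the stratification factors, baseline bacteriuria and, if repeated, visit. Baseline bacteriuria is already on the list of candidate covariates but is not guaranteed a place in the final model.
- Report specimens received and prevalence by arm and visit, so that any difference in specimen return can be seen. The model alone does not deal with it.

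The cost is a change of wording in the protocol or analysis plan. If the analysis plan already specifies a binomial model, only the protocol sentence needs to be aligned with it. No new data are needed, because the specimens, including baseline, are already scheduled.
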